### Randomization

Each child will be randomized to either the real (intervention) or sham (control) tDCS arm of the study. The randomization will be done by means of sealed envelopes constructed by the study biostatistician using a random number generator. The study coordinator will assign envelopes, in numerical order, to the subjects upon their randomization.

### Blinding

The investigator who performs the testing, the CIMT interventionists and the physician who does the evaluations will be blinded to the treatment arm as will the child/caregiver/family. The study biostatistician, study coordinator and principal investigator (PI) will be unblinded. The following procedure will be employed:The study biostatistician will provide sealed envelopes to the study coordinator.The study coordinator will share the group assignment with the principal investigator in a secure private room, in the absence of the physician, research tester, subject legal guardian and subject. The Medical Monitor to the study will have access to the group assignment.Blinding is applied through designated settings on the tDCS machine of sham or real tDCS. The unblinded investigator who administers the tDCS (PI: [name]) will, during the intervention, switch the setting on the tDCS device to the designated placebo setting, hidden from view of the subject. For the first 30-seconds of either setting, a gradual “ramp-up” sensation of the stimulation occurs. This is built into the machine for both settings. However, for the sham stimulation, the sensation then abates, and not until the end of the 20-minute session does the subject receiving the 30-seconds of “ramp-down” sham once again experience the sensation. The sensation then occurs and “ramps-down” the amperage until the machine turns off.Information on subject group assignment will be logged and stored in a designated locked cabinet at the study coordinators office.

Outcome Assessments. We incorporated the body function/structure and activity/participation domains of the International Classification of Functioning, Disability and Health [2727].

### Primary outcome measure

The Assisting Hand Assessment (AHA) scaled score will be used as the primary outcome measure as a test of unilateral limb dysfunction; it is based on a child’s usual performance in relevant activities. This test uses a standardized video-recorded play session. Activity is assessed on 22 items using a 4-point rating scale. The range of raw scores is 22–88 points, with higher scores indicating better ability. Excellent interrater (0.97) and intrarater (0.99) reliability has been found using this tool and it has been found to have high validity in use with children[28-30]

### Secondary outcome measures

The Canadian Occupational Performance Measure (COPM) is an individualized outcome measure used to detect changes in the self-perception of the client’s performance and satisfaction over time by identifying difficulty in performance of specific activities [31, 32]. The tool is a self-reported ordinal scale score which encompasses domains in impairments, body structure, activity, activity limitations, participation restrictions and environmental factors which an individual experiences. Test-retest reliability has been found to be strong in the domains of performance (r = 0.89) and satisfaction (0.88). Grip strength will also be measured using hand dynamometry[33].

#### Sample size/power

Power calculations for the primary outcome measure AHA scaled score difference between pre- and post-test measurements used the sample size formula for normally distributed statistics with a type I error level of α (2-sided test) and power of (1-β):$$ n=\frac{V{\left({Z}_{\left(1-\propto /2\right)}+{Z}_{\left(1-\beta \right)}\right)}^2}{\varDelta^2} $$

where Δ denotes the minimal clinically important difference (MCID) to detect, n denotes the sample size per group, and V denotes the variance of the test statistic. For ANCOVA analyses, V = 2(σ^2)(1-ρ^2) where σ^2 is the (average) variability and ρ is the (average) correlation between pre- and post-treatment measurements [34, 35]. Power (1-β) was computed for 10 patients per treatment group across a range of possible values for the correlation with alpha equal to 0.05. These are computed for an MCID of 2.4, and for the rTMS/CIMT study treatment effect of 5.4, which is considered a reasonable estimate for this tDCS exploratory study [36]. The standard deviation from the rTMS/CIMT study was used as an estimate for the power calculations and was equal to 4.7. In addition, 1.5 times the standard deviation of the rTMS/CIMT study was also used in the power calculations to provide power estimates within a conservative standard deviation. The correlation between pre- and post-treatment AHA scores in the rTMS study was 0.97. Based on a correlation of 0.8 and using the conservative standard deviation of 7.1, we will have 80 % power to detect the difference of 5.4 between treatment groups.

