### Study design

The study will use a randomized, sham-controlled, pretest-posttest-follow up design involving two groups of 10 children with hemiparesis and unilateral infarct or periventricular leukomalacia as confirmed by MRI (total sample size = 20). (Fig. 1). This protocol is registered on clinicaltrials.gov (# NCT02250092)

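### The stated 80% power for a 5.4-point AHA difference is a large-sample figure; the planned ANCOVA in 20 children gives about 74–76% on the same inputs

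*Protocol article*

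**What the plan says.** All the inputs are in the Sample size/power section of the protocol article.

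- **Method.** The calculation "used the sample size formula for normally distributed statistics with a type I error level" α, two-sided. The variance term for ANCOVA is V = 2σ²(1−ρ²), with ρ the pre/post correlation.
- **Size.** Power "was computed for 10 patients per treatment group", "across a range of possible values for the correlation with alpha equal to 0.05". The Study design section agrees: "two groups of 10 children with hemiparesis".
- **Differences considered.** "These are computed for an MCID of 2.4, and for the rTMS/CIMT study treatment effect of 5.4".
- **SD.** 4.7 from the earlier rTMS/CIMT study, and 1.5 times that (given as 7.1) as a cautious value.
- **Correlation.** "The correlation between pre- and post-treatment AHA scores in the rTMS study was 0.97". The quoted result uses 0.8 instead.
- **Result.** "using the conservative standard deviation of 7.1, we will have 80" percent power for 5.4 points.

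The Statistical Analysis paragraph plans to compare mean pre-to-post change between groups with adjustment for baseline in the manner of ANCOVA, at the 0.05 level.

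**The concern.** The formula treats the residual variance as known and the baseline slope as costless. With hundreds of patients that makes no practical difference. With 20 children the test is referred to a t distribution with 20 − 3 = 17 degrees of freedom, and part of the information goes on correcting whatever baseline imbalance arises by chance. Both lower the power below the formula's value.

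Two features of the same paragraph add to this. Power is said to have been computed for 2.4 as well as 5.4, but only the 5.4 result is given, and 5.4 is 5.4/2.4 = 2.25 times the minimal clinically important difference (MCID). The article also does not say whether 4.7 is the SD of AHA scores or of their change, although V = 2σ²(1−ρ²) is correct only for scores.

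At stake is how the AHA comparison is described to readers. The only power figure they are given overstates what the planned test delivers in the stated scenario.

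**Working it through.** **Inputs** (Sample size/power): n = 10 per group, Δ = 5.4, σ = 7.1, ρ = 0.8, two-sided α = 0.05. The analysis (ANCOVA) is from the Statistical Analysis paragraph.

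**1. The article's own figure.**
- Residual SD = 7.1 × √(1 − 0.8²) = 7.1 × 0.6 = 4.26.
- V = 2 × 7.1² × 0.36 = 36.30.
- Δ/√(V/n) = 5.4/√3.630 = 2.834.
- Power = Φ(2.834 − 1.960) = 80.9%. The stated 80% reproduces.

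**2. The planned test, before baseline imbalance.** The noncentrality is the same 2.834. The reference is t with 17 df, critical value 2.110. Noncentral t power = **76.2%**.

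**3. Allowing for chance baseline imbalance.** The ANCOVA variance of the group difference is σ_res²(2/n + d²/SSW), where d is the difference in baseline means and SSW the within-group sum of squares of baseline. Averaging the 17-df power over simulated baselines gives **about 74%** (73.8%). Using the average inflation factor 1 + 1/16 instead gives 73.6%.

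**4. Difference detectable with 80% power.** With imbalance allowed for, power at 5.8 is 79.6%, so about **5.8**. Without it, power at 5.7 is 80.5%. On the simpler calculation of step 2, 11 per group would be needed for 80% at 5.4 (80.5%).

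**5. The MCID in the same scenario.** For Δ = 2.4 the article's formula gives 24%. The 17-df test gives 22%, or 21% with imbalance.

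**6. How cautious the scenario is.** Power for 5.4 by the method of step 3, reading the SD as an SD of scores:

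| SD | ρ | Power |
|---|---|---|
| 7.1 | 0.80 | 74% |
| 7.1 | 0.85 | 84% |
| 7.1 | 0.90 | 95% |
| 4.7 | 0.80 | 97% |

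For Δ = 2.4, power is about 41–42% at SD 4.7 with ρ = 0.8, and about 81% at SD 7.1 with ρ = 0.97.

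**7. What 4.7 describes.**
- Read as an SD of scores with ρ = 0.97, the SD of change is 4.7 × √(2 × 0.03) = 1.15. An effect of 5.4 would be 5.4/1.15 = 4.7 such SDs, which looks odd.
- Read as an SD of change (an assumption), the score SD is 4.7/√0.06 = 19.2 and the ANCOVA residual SD is 4.7 × √((1 + 0.97)/2) = 4.66. That exceeds the 4.26 used in step 1 as the cautious value. The factor (1−ρ²) would then largely count the correlation twice.
- Under this second reading, at ρ = 0.97, power for 5.4 is about 66–69% with SD 4.7 and about 35–37% with the 1.5-fold inflation. The lower end of each range allows for baseline imbalance.

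**The case against.** The strongest reply is that nothing has been miscalculated. The formula is named, the inputs are given, and the result follows. The quoted scenario also sits in a deliberately pessimistic corner: the SD is inflated by half and the correlation is lowered from 0.97 to 0.8. At SD 7.1, a correlation of about 0.83 already restores 80% under the exact method, so the approximation error is smaller than the margin built in. This stands, and it limits the severity. It does not rescue the figure, because 80% is claimed for that very scenario and the planned test does not deliver it there.

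Three stronger readings are tempting, and the document does not support them.

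- **That true power is about 35%.** This needs 4.7 to be an SD of change. The article describes σ² only as average variability, beside a formula that is correct for scores. The oddity of a 1.15-point SD of change is suggestive, but it presumes that 4.7 and 0.97 describe the same children and time points. Only the cited rTMS/CIMT study could settle it, and it is not at hand.
- **That the trial can say almost nothing at its MCID.** The 21–22% belongs to the cautious scenario; step 6 shows far higher power under others. Quoting one result from a grid is also ordinary in a condensed article, and the study is called exploratory.
- **That a non-significant result will be taken as evidence against benefit, or that drop-out is mishandled.** No passage says the former. On the latter, one loss per arm would bring power to about 68%, but nothing in the article supports that particular loss over a two-week intervention.

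**Conclusion.** The point holds in a limited form. On the article's own inputs, the planned ANCOVA has about 76% power for 5.4 points, or about 74% with chance baseline imbalance. That is 4 to 6 points below the stated 80% and 5 to 7 below the formula's 80.9%. The cause is a large-sample formula applied to 20 children.

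The result assumes normal errors, equal variances, all 20 children analysed, and 7.1 as an SD of scores. The question about 4.7 remains a request for clarification: it could matter more than the approximation, but it cannot be decided from the document. Severity is moderate. Design, sample size and analysis are unaffected.

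**What to change.** 1. Restate the power: with 10 per group, SD 7.1 and correlation 0.8, the baseline-adjusted ANCOVA (t, 17 df) has about 74–76% power for 5.4 points, or 80% power for about 5.8.
2. Give the figure for 2.4 in the same scenario (about 21–22%). Say that the scenario uses an inflated SD and a correlation below the 0.97 observed, so that neither number is taken for a best estimate.
3. State that 4.7 is the SD of AHA scores, if it is. If it is an SD of change, replace the variance term (residual SD = SD of change × √((1+ρ)/2)) and quote the resulting power.

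The cost is a few sentences and one look-up in the earlier study's data. No patients are added. The published power becomes somewhat less favourable.

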#### Study protocol

Children will be randomized into two groups: real tDCS/CIMT (intervention) or sham tDCS/CIMT (control). The children will receive 10 continuous weekday sessions of tDCS and CIMT. (Fig. 2) To clarify, we will include only children in whom we can elicit a motor evoked potential (MEP) using TMS applied to the ipsilesional hemisphere. Although by doing so we limit greatly the number of children whom we can include, such conservatism is necessary to proceed in a safe and informed manner with sufficient awareness of the functional topography of each subject’s brain.

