### Hypotheses

Children in the tDCS/CIMT group will show significantly greater excitability in the ipsilesional hemisphere than will controls.Changes in brain excitability and reorganization will correlate with positive changes in motor function.

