Excitability Measurements using TMS*.* TMS (Magstim, Dyfed, UK) will be used to measure corticospinal excitability in the ipsilesional and contralesional hemispheres. TMS will be delivered with a 70-mm figure-of-eight coil, tangential to head with handle aligned 45 degrees lateral. The assessment will incorporate single-pulse motor threshold, 1 mV and cortical silent period testing. TMS measurements of cortical excitability guided by stereotactic neuronavigation (Brainsight, Rogue Research, Montreal, QC, Canada), will be employed to create a map of the motor cortex from anatomical MRI images obtained at the CMRR. The co-registration of the TMS coil position on the head with the MRI obtained image of the brain anatomy will allow precision in children who have neurologic lesions. All TMS testing will occur in the UMN CTSI by the PI. For this, the child will be seated in a child-sized reclining chair. Surface electromyographic (EMG) electrodes will be attached over the first dorsal interosseous muscles bilaterally, which will record the motor evoked potentials (MEP) resulting from the magnetic stimulation to the M1 region of each hemisphere. Next, the resting motor threshold (RMT) for TMS activation of the target muscle will be determined, and the location of the hotspot defined. If a threshold cannot be elicited within at least the contralesional hemisphere (i.e., no hotspot), the subject will be excluded from the study as position of the tDCS electrodes will be influenced. The RMT will be defined as the lowest amount of stimulation inducing an MEP of at least 50uV on at least 3 of 5 stimulations Cortical excitability will also be tested by administration of 10 TMS pulses, at the minimum stimulus intensity to produce MEPs of 1 mV [44].

CSP will be determined by the subject exerting finger extensor contraction at approximately 30 % of maximum, as guided by a force tracing on a computer display, while a single TMS pulse at an intensity of 150 % of RMT is delivered to the ipsilesional M1 cortex [45, 46]. The resultant CSP will be measured from the onset of the first peak of the MEP to resumption of surface EMG activity with a threshold value of 50 % mean prestimulus amplitude [47].

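### The article states two different motor evoked potential (MEP) rules for entry, so a child with a contralesional response only is eligible in one place and ineligible in another

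*Protocol article*

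**What the plan says.** The Protocol article deals with MEP eligibility in three places.

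- **Inclusion criteria.** An MEP from the contralesional side is the minimum. Responses from both sides are acceptable but not required.
- **Excitability measurements using TMS** (a paragraph under Rationale for use of tDCS). The exclusion trigger matches that minimum: "If a threshold cannot be elicited within at least the contralesional hemisphere (i.e., no hotspot), the subject will be excluded from the study". The reason given is that electrode position depends on it.
- **Study protocol.** Introduced as a clarification: "we will include only children in whom we can elicit a motor evoked potential (MEP) using TMS applied to the ipsilesional hemisphere". The text accepts that "by doing so we limit greatly the number of children whom we can include" and defends this as caution needed for safety and for knowing each child's functional brain topography.

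Two other places depend on the rule. The section on the tDCS/CIMT intervention group puts the cathode over the contralesional motor hotspot. The first hypothesis under the secondary objective reads: "Children in the tDCS/CIMT group will show significantly greater excitability in the ipsilesional hemisphere than will controls".

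**The concern.** Entry rules decide who is randomised and, here, which children may receive brain stimulation. Two statements set the minimum on the contralesional side and the third sets it on the ipsilesional side. Staff screening a child with a contralesional response only would get opposite answers from different pages. Nothing in the article says which statement governs.

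The third statement is hard to dismiss as loose wording, because it gives a reason for the restriction and admits its cost in numbers. If the word ipsilesional is a slip, that section is wrong. If it is meant, the Inclusion criteria and the TMS paragraph admit children whom the article says should be kept out.

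Three things are at stake: the population to which a 20-child trial applies, the safety reasoning attached to one version of the rule, and which children can contribute to the ipsilesional excitability comparison.

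**Working it through.** **1. Apply each statement to the four possible MEP patterns.**

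| MEP pattern | Inclusion criteria | TMS paragraph | Study protocol |
|---|---|---|---|
| Both hemispheres | meets | not excluded | meets |
| Contralesional only | meets | not excluded | **fails** |
| Ipsilesional only | fails | excluded | **meets as worded** |
| Neither | fails | excluded | fails |

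The second row is the direct contradiction. The third row shows that the Study protocol sentence, taken alone, does not secure the contralesional hotspot that the TMS paragraph and the intervention section need for the cathode.

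**2. Which measures need an ipsilesional MEP.** The definitions are in the TMS paragraph.

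- Resting motor threshold (RMT): "The RMT will be defined as the lowest amount of stimulation inducing an MEP of at least 50uV on at least 3 of 5 stimulations". Without an MEP there is no threshold.
- 1 mV test: ten pulses "at the minimum stimulus intensity to produce MEPs of 1 mV". Without an MEP there is no such intensity.
- Cortical silent period (CSP): "a single TMS pulse at an intensity of 150 % of RMT is delivered to the ipsilesional M1 cortex", timed from the MEP. Without an MEP both the intensity and the starting point are undefined.

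The same paragraph measures excitability in both hemispheres, and the MRI paragraph provides resting-state fMRI and DTI. A child with no ipsilesional MEP therefore loses the ipsilesional TMS measures and keeps the contralesional TMS and imaging measures.

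**3. The article's own power figure.** Inputs from Sample size/power: n = 10 per group, difference 5.4, SD 7.1, correlation 0.8, two-sided alpha 0.05.

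- V = 2 × 7.1² × (1 − 0.8²) = 2 × 50.41 × 0.36 = 36.30
- Standard error = √(36.30/10) = 1.905
- 5.4/1.905 = 2.834, and 2.834 − 1.960 = 0.874, which gives power of 80.9%

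The stated 80% is reproduced. No MEP quantity enters the formula, so the contradiction leaves it unchanged.

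**4. Illustration for the ipsilesional comparison.** Let q be the share of each arm with a measurable ipsilesional MEP. The article gives no value, so q is an assumption shown over a range, taken as equal in both arms. With 10q per arm, the detectable difference at 80% power in SD units is (1.960 + 0.842) × √(2/(10q)).

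| q (assumed) | Measurable per arm | Detectable difference (SD) |
|---|---|---|
| 1.0 | 10 | 1.25 |
| 0.8 | 8 | 1.40 |
| 0.6 | 6 | 1.62 |
| 0.5 | 5 | 1.77 |
| 0.4 | 4 | 1.98 |

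The row q = 1.0 is also what a rule requiring an ipsilesional MEP gives if all 20 children are still recruited.

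**The case against.** The strongest reply is that the statements can be combined. Excluding children without a contralesional threshold and also those without an ipsilesional MEP amounts to requiring responses from both hemispheres, and the Study protocol sentence is offered as a clarification. This reconciles the TMS paragraph with the Study protocol section. It does not reconcile either with the Inclusion criteria, which expressly accept one hemisphere. The combined rule is stated nowhere, so the conflict stands.

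The reply is right about several stronger readings that a reader might infer.

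- *Children without an ipsilesional MEP would have no data for the secondary objective.* Only their ipsilesional TMS measures are undefined. The planned association analysis covers brain reorganisation as well as excitability, and their contralesional TMS and imaging data can still enter it.
- *Selective missingness would bias the treatment comparison.* MEP status is an entry criterion and so a pre-treatment trait. Restricting on it costs precision and generalisability but does not in itself bias the randomised contrast.
- *The loss is known to be large.* The article says its stricter rule limits inclusion greatly but gives no rate, so any figure is illustrative.

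It may also be said that analysis sets belong in the analysis plan. That is fair, and their absence from the article is not the point here. The contradictory eligibility text is in the article itself.

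**Conclusion.** The contradiction holds. A child with a contralesional MEP only is eligible under the Inclusion criteria and the TMS paragraph and ineligible under the Study protocol section, and no other text settles it. The Study protocol sentence also leaves the contralesional hotspot unaddressed.

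The importance rests on eligibility and on the safety reason that the article attaches to one version of the rule. It does not rest on a demonstrated loss of power. The statistical consequence is conditional: it arises only if children without an ipsilesional MEP are enrolled, and it is confined to ipsilesional RMT, 1 mV and CSP. Its size cannot be derived from the article, and the range from 1.25 to 1.98 SD depends entirely on the assumed q. The AHA, COPM, grip strength and imaging outcomes do not need an ipsilesional MEP.

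**What to change.** Reconcile the Inclusion criteria, the Study protocol section, the TMS paragraph and the tDCS/CIMT intervention section into one identically worded rule that states the MEP requirement separately for each hemisphere. The investigators and medical monitor must decide which rule applies, and this review takes no position on that. Deleting the contralesional wording from the Inclusion criteria and the TMS paragraph would not be enough, because the cathode placement depends on the contralesional hotspot.

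If children without an ipsilesional MEP remain eligible, define the ipsilesional excitability comparison on children with a baseline ipsilesional MEP, and acknowledge the cost in precision and generalisability. One sentence in the analysis plan is enough.

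The cost is a wording change and possibly that one sentence. No new procedure is needed, since TMS testing of both hemispheres is already planned.
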